**Table 2 T2:** **Follow**-**up flowchart**

	**Intake**	**Operation**	**6w**	**3 m**	**6 m**	**8 m**	**12 m**	**24 m**
Demography & diagnosis	X							
Neurological examination	X	X	x		x		x	x
Informed consent	X							
MRI	X						x	
NDI	X		x	x	x	x	x	x
VAS pain/tinglings	X		x	x	x	x	x	x
SF-36	X		x	x	x	x	x	x
IPQ-K	X							
Perceived recovery	X		x	x	x	x	x	x
Health state utility VAS	X		x	x	x	x	x	x
DS-14	X		x	x	x	x	x	x
EuroQol	X		x	x	x	x	x	x
Diary	X		x	x	x	x	x	x
Re-operation			x	x	x	x	x	x
Complication			x	x	x	x	x	x

Overview of follow-up moments and received information (for explanation: see text).

#### Primary outcome measure

The primary outcome parameter is severity of main complaint: VAS pain or tingling sensations. The disabling intensity in the arm will be measured with a 100 mm horizontal VAS; “no pain or tingling sensations” at 0 mm and “the most terrible pain or tingling sensations I can imagine” at 100 mm [26,27]. During each visit the VAS arm pain will be scored. Additionally, the time of complaints will be scored as the time between the first general practitioners visit for this pain in the arm till the moment of randomisation, measured in weeks.

#### Secondary outcome measures

1. Neck Disability Index (NDI). Although the NDI is a score to monitor complaints of cervical myelopathy, it gives a reliable impression of the disability of the patient with respect to daily activities [28,29]. The scores of the items are added up and transformed into a scale of 0 to 100. A higher score reflects a better health condition.

2. VAS pain or tingling sensations in the arm at different time points (intake, 6 weeks and 3, 6, 8, 24 months).

3. VAS pain in the neck. The pain intensity in the neck will be measured with a 100 mm horizontal VAS at different time points (intake, 6 weeks and 3, 6, 8, 12, 24 months).

4. Short Form-36 (SF-36). The SF-36 will be used as a generic quality-of-life questionnaire. The questionnaire relates to the analysis of the general functional status of patients. The scores of the different topics are added up and transformed into a scale of 0 to 100. A higher score reflects a better health condition. The different topics can be summarised in a physical and psychological main domain.

5. Illness Perceptions Questionnaire – short form (IPQ-K). The Brief Illness Perceptions Questionnaire is translated from English to Dutch and adapted for differences in culture [30]. This questionnaire represents the way a patient copes with his complaints, and it gives insight in the functioning of a patient.

6. Perceived recovery. To measure perceived recovery a seven-point Likert scale will be used [31]. The scores on this scale vary from ‘completely recovered’ to ‘worse than ever’. The scales will be completed by the patient, research nurse, and the neurologist or neurosurgeon.

7. Health state utility VAS. Patients will assess how they value their health using a VAS ranging from 0 = as bad as death to 100 = perfect health.

8. DS-14. This Dutch questionnaire determines the extent of ‘Distressed-personality’ of the patient. A type D personality is defined in medical psychology as the co-existent presence of both negative affectivity (e.g. worrying, irritability, gloom) and social inhibition (e.g. reticence and a lack of self-assurance). The questionnaire consists of seven questions concerning negative affectiveness and seven questions concerning social inhibition. Individuals that score on both dimensions 10 or higher are being classified as having a type D personality. A type D personality has been demonstrated to have a negative influence on outcome of disease [32,33].

9. EuroQol – EQ-5D. The EuroQol (EQ-5D) will be used to value the patients’ health for the cost utility analysis. As indicated by the name the tool measures five dimensions: mobility, self-care, daily activities, pain/discomfort, and anxiety/depression. Each domain is rated as having no problems, some problems or extreme problems.

10. Cost diaries, including absenteeism, will be filled out by the patients during follow-up.

11. MRI. MRI findings at baseline and after 1 year will be compared: extrusion or protrusion, the difference in size of the disc herniation, nerve root compression, and, if operated, presence of scar tissue will be registered. The data will be registered using standardised CRFs, which will be filled out by the local radiologist and neurosurgeon.

12. Frequency of (re)operation in the conservative group and frequency of reoperation in the surgery group.

13. Frequency of complications.

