### Baseline data

The baseline questionnaires and demographics will be registered before randomisation. Also the preferences of patients and doctors will be registered using a 5-point scale varying from ‘strong preference for surgery’ to ‘strong preference for conservative treatment’.

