#### Secondary outcome

Secondary outcomes will be analysed for differences between groups with linear mixed models similar to the main endpoint. Furthermore, we will investigate whether potential prognostic variables (gender, age, presence of neck pain, more neck pain than arm pain, Valsalva manoeuvre test, Spurling test, shoulder abduction test, type of personality based on DS-14 and based on IPQ-K, anterior or posterior approach, smoking, neurological deficits (strength on an 1–5 Medical Research Council (MRC) scale and sensibility), duration of the symptoms, Quetelet index) are associated with the difference between the treatment arms in the primary endpoint. This will be carried out by adding a potential prognostic variable and its interaction with the treatment arm to the linear mixed model.

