## Conclusion and Discussion

The objective of the current trial is to study the effectiveness of the surgical intervention and prolonged conservative care for CRS. Secondary, an analysis of cost-effectiveness, timing of surgery and prognostic factors in favour of one of the strategy arms will be performed. The only two other randomised trials on this subject enrolled a limited number of patients and did not measure these secondary outcomes.

The CASINO trial is performed using ‘usual care’ and has a pragmatic design. It acknowledges that sometimes it may not be possible to postpone surgery for every conservative care patient until 6 months after allocation and that some patients will recover before surgery is performed in the surgical group. In these cases we consider it infeasible and unethical to hold on to the randomised treatment. Because of the intent-to-treat analysis, these cases will be analysed according to the originally allocated randomisation arm. Methodologically, this is the appropriate way to compare two healthcare strategies, as opposed to two treatments.

We hypothesise that prolonged conservative care will have comparable results as surgery on primary outcome (i.e. VAS pain or tingling sensations) after one year of follow-up. However, due to the risks and the costs of surgery we hypothesise that prolonged conservative care will be more (cost-) effective with less adverse events.

We hypothesise that those patients who endured symptoms for a longer time, would benefit from surgery. If true, it would be interesting to investigate whether there is a cut-off time-point after which surgery demonstrates a better result.

Finally, the predefined subgroup analyses may provide us with parameters, which can predict preference for one of the two treatment strategies. It is hypothesised that patients demonstrating more neck pain than arm pain or a type D personality will have better outcomes with conservative therapy.

The results of the present study will provide insight in the results of surgery at an early phase and of prolonged conservative care. This information will be useful in shared decision-making for choosing the most appropriate treatment for radicular cervical syndrome.

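### Two hypothesised effect modifiers are worded as yes/no cuts of scores collected at intake; adding a prespecified one-degree-of-freedom graded interaction for each would be a cheap improvement

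*Protocol article*

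**What the plan says.** Under Secondary outcome measures, item 8, the protocol article describes the DS-14 as two scores: "The questionnaire consists of seven questions concerning negative affectiveness and seven questions concerning social inhibition". It then reduces them to one label: "Individuals that score on both dimensions 10 or higher are being classified as having a type D personality".

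The Statistical analysis section, under Secondary outcome, lists personality type from the DS-14 among the candidate modifiers, together with "presence of neck pain, more neck pain than arm pain". The method is the same for each: "This will be carried out by adding a potential prognostic variable and its interaction with the treatment arm to the linear mixed model".

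The Conclusion and Discussion states a hypothesis for these same two categories, namely that "patients demonstrating more neck pain than arm pain or a type D personality will have better outcomes with conservative therapy". The only other listed modifier with a stated hypothesis is duration of symptoms.

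The finer measurements already exist. For the neck, "The pain intensity in the neck will be measured with a 100 mm horizontal VAS at different time points", intake included. For the arm, "The disabling intensity in the arm will be measured with a 100 mm horizontal VAS", and Table 2 schedules it at intake. Table 2 also lists the DS-14 at intake, and under Baseline data "The baseline questionnaires and demographics will be registered before randomisation".

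**The concern.** A cut discards the distances between patients. If more neck pain than arm pain is read as a comparison of the two VAS scores, a patient with neck 51 and arm 50 falls in a different group from one with neck 50 and arm 51, but in the same group as one with neck 90 and arm 45. Type D is a double cut, at 10 on each of two scores.

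For duration, the Sample size section keeps the continuous scale and models the change in treatment effect per month. The article gives no reason for handling the other two hypothesised modifiers differently.

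The Discussion hopes that the subgroup analyses will yield parameters that predict which strategy suits a patient. If the benefit shifts gradually with the score, a test on the cut has less chance of showing it, and a null result could be misread as no modification.

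**Working it through.** **1. The plan's own interaction calculation.** The Sample size section gives SD of VAS 30 mm, SD of duration 25 months, a target of 4 mm per year (4/12 = 0.333 mm per month), two-sided α = 0.05 and power 0.80:

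n − 1 = (1.96 + 0.84)² × 2 × (30/25)² / 0.333² = 203.2, so n ≈ 204 per arm against 200 stated.

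The stated figure is reproduced within rounding. It is the only interaction the plan powers, so its 80% serves below as a reference point. With 200 per arm, the standard error of the interaction per SD of a continuous modifier is √2 × 30/√199 = 3.0 mm. Power of 80% therefore needs the treatment effect to change by about 2.80 × 3.0 = 8.4 mm per SD, close to the duration target of 0.333 × 25 = 8.3 mm per SD. Nothing in the article says that either of the two other modifiers is that strong.

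**2. Information kept by a cut.** Assume a normally distributed score and a treatment effect linear in it. Cutting the score so that a share p falls in the group shrinks the interaction z-value by r = φ(z_p)/√(p(1−p)). The information kept is r², and power is Φ(2.80 r − 1.96).

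| p | r | r² | Power, from 80% |
|---|---|---|---|
| 50% | 0.798 | 0.64 | 61% |
| 40% | 0.789 | 0.62 | 60% |
| 30% | 0.759 | 0.58 | 57% |
| 20% | 0.700 | 0.49 | 50% |
| 10% | 0.585 | 0.34 | 37% |

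**3. Scenarios nearer to the two modifiers.** The article gives no baseline distributions, so all of these are assumptions.

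- *Neck versus arm:* arm VAS mean 65–70 and at least 40, neck VAS mean 45–60, SD 20–25, correlation 0–0.5. In simulation, 9–37% have more neck than arm pain, the cut keeps 31–62% of the information in the difference score, and power falls from 80% to about 35–59%.
- *Type D:* DS-14 scores with mean 7–10, SD 6, correlation 0.3–0.5. In simulation, 18–37% are type D, the cut keeps 45–63% against the sum or product of the scores, and power is 47–60%. A second set of simulations (correlation 0.2–0.6, prevalence 15–40%) gives 55–60% if the product drives modification and 39–56% if the sum does.

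**4. Dependence on the reference power.** Replace 2.80 by 1.96 + z(reference power) and use 31–63% information.

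- Reference 20%: 1.96 − 0.84 = 1.12. Power on the cut is Φ(1.12√0.31 − 1.96) = 9% to Φ(1.12√0.63 − 1.96) = 14%, a loss of about 6–11 points.
- Reference 10%: 1.96 − 1.28 = 0.68. Power on the cut is about 6–8%, a loss of about 2–4 points.

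**5. Scale of the yes/no test.** Assume 10% loss to follow-up here too (180 per arm) and a 20% subgroup. The interaction SE is √2 × 30 × √(1/36 + 1/144) = 7.9 mm. The difference detectable with 80% power is 2.8 × 7.9 ≈ 22 mm, against the 15 mm main-effect target.

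**6. How the DS-14 term is specified.** Entering both scores and their product as a joint test uses three degrees of freedom. At the noncentrality that gives 80% with one degree of freedom, the three-degree test has about 64%. Most of the advantage over the cut (47–60%) is then gone, so the graded alternative has to be a single term.

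**The case against.** The strongest reply is that the category is the hypothesis. The article presents type D as a recognised construct, the joint presence of two traits, with cited evidence on outcome, and the Discussion hypothesises about that group by name. Testing the named group answers the stated question. This stands, and it is why type D should stay in the plan.

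Second, the coding is partly inferred. The DS-14 sentence is a scoring definition under outcome measures, and the analysis section says only that a variable and its interaction will be added. It does not say that the neck/arm modifier is a cut at zero of two VAS scores. A reader might infer that the plan fixes binary coding for both. The wording is categorical throughout, but the article does not state the coding, and a full analysis plan may do so.

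Third, the size depends on inputs that the documents do not give. A reader might infer that the trial will lose 20 or more points of power. That holds only if modification is graded and the full-scale test has power near 80%, and neither is stated. Under a step at the cut, the continuous test is the weaker one by the same factor. The Discussion even contemplates a cut-off for duration, so a threshold cannot be ruled out.

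What survives is that the finer scores are collected before randomisation and no graded version of either modifier is mentioned.

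**Conclusion.** The point holds as a low-severity, conditional improvement. If modification is graded, the worded cuts keep roughly 30–65% of the information; an 80% one-degree-of-freedom test would become about 35–61%, with smaller losses at low reference power. These figures rest on assumed baseline distributions, linearity and a reference power borrowed from the duration question. The document supports neither a fixed loss of 20 points nor a claim that the categories are wrong. The primary comparison, the sample size and the duration analysis are unaffected.

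**What to change.** In the Statistical analysis section, under Secondary outcome:

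- Test the neck/arm modifier as baseline neck VAS minus baseline arm VAS (mm), with its interaction with treatment estimated at 12 months (one degree of freedom). Keep the yes/no group to present the treatment effect by group and as a sensitivity analysis.
- For DS-14, keep type D as the stated hypothesis. Add one prespecified graded term, for example the product or the sum of the two baseline scores, by treatment. Do not use a joint three-term test.

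If graded scores are already intended, saying so settles the matter. The cost is a sentence or two of analysis wording, with no new data. The downside is a linearity assumption that is less sensitive to a pure threshold effect, which the retained yes/no analyses cover.

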### Sample size

For the primary research question, the sample size is based on the standard deviation of VAS arm pain, which is estimated between 25 and 30, as reported by Persson after 1 year of follow-up [20]. If we consider an α = 0.05 and a power of 90%, and we take 15 mm difference in VAS pain in the arm as clinically relevant, then we need 100 patients in both groups (including a 10% compensation for lost to follow-up) in a worst case scenario of a standard deviation of 30 to show such a difference as statistically significant under the null hypothesis. Because the analysis for the secondary question requires more patients than the primary research question, the sample size is chosen with regard to the secondary research question. In order to investigate the modifying effect of the (pre-randomisation) duration of pain (X, in months) on the treatment effect (T) a covariance-analysis will be performed with the VAS measured after 12 months follow-up as a dependent variable and T, X and the interaction T*X as independent variables. The coefficient of T*X represents the increase (or decrease) of the treatment effect per month duration of pain on baseline. The standard error of the slope of this regression line is $\sqrt{\left(1-\rho^{2}\right)}\sigma_{\mathrm{vas}}/\left(\sqrt{n-1}\sigma_{x}\right)$, in which ρ is the correlation between the duration of pain at baseline and the VAS after 12 months follow-up, σ_VAS_ the SD of the VAS after 12 months follow-up and σ_X_ the SD of the duration of pain at baseline. Based on the RCT by Persson [20] the σ_VAS_ is estimated conservatively at 30 mm and the SD of the duration of pain at baseline conservatively at 25. We are not informed about the correlation, but ρ = 0 leads to a conservative estimate of the standard error of the slope. Because this correlation is probably small, the overestimation of the sample size is probably limited (for instance 1% if ρ = 0.1 or 4% if ρ = 0.20). The number of patients needed for a power 1-β = 0.80 and two-sided significance level of α = 0.05 can be calculated as $n_{\mathrm{pergroup}}-1={\left(1.96+0.84\right)}^{2}\cdot 2\sigma^{2}/\Delta^{2}$, in which σ = σ_VAS_/σ_X_ and Δ is the increase of the difference in slope per month. An increase in the difference in slope of 4 mm per year duration of pain at baseline is considered as clinically relevant. According to the formula above, 200 patients per study arm are needed, adding up to a total of 400 patients.

The number of 200 patients in both groups that is needed for the second primary research question also has the advantage that it adds some additional power for subgroup analyses. By taking 200 patients per group the power for the first research question rises to above 99% for a SD of 30 and a difference of 15.

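### The treatment-by-duration calculation that fixes the 400 patients omits the 10% loss allowance used for the main comparison; with that loss its power is about 75% at a VAS SD of 30, not 80%

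*Protocol article*

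**What the plan says.** All of this is in the protocol article, mostly under Sample size.

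- For the main comparison at one year, the section arrives at 100 patients per group, "including a 10% compensation for lost to follow-up". The inputs are a 15 mm difference, 90% power and an SD of 30, the top of the range of 25 to 30 that it gives.
- It then says that the trial size is chosen for the other question, whether the treatment effect depends on duration of pain. The covariate is "the (pre-randomisation) duration of pain (X, in months").
- Significance level and power: "The number of patients needed for a power 1-β = 0.80 and two-sided significance level of α = 0.05 can be calculated as" a formula in the two SDs and the slope difference. The formula has no loss term.
- Inputs: the SD of the 12-month VAS "is estimated conservatively at 30 mm and the SD of the duration of pain at baseline conservatively at 25", with a correlation of zero between duration and VAS.
- Target: "An increase in the difference in slope of 4 mm per year duration of pain at baseline is considered as clinically relevant".
- Result: "According to the formula above, 200 patients per study arm are needed, adding up to a total of 400 patients". The closing paragraph of the section repeats 200 per group as the number needed. The abstract gives 400 as the sample size.

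Under Primary outcome measure, duration is recorded as "the time between the first general practitioners visit for this pain in the arm till the moment of randomisation, measured in weeks".

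**The concern.** Both calculations concern the VAS at 12 months in the same patients, so the same loss should apply to both. The allowance is given to the calculation that does not determine the trial size and withheld from the one that does. Since 200 is slightly below what the formula returns, it cannot contain a hidden allowance.

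By the plan's own account the main comparison needed only 100 per group. The second 200 patients are there for the duration question, and the stated 80% is what justifies them. If the interaction turns out null, readers will judge that result against a power which, on the plan's base-case inputs and with its own expected loss, the design does not quite have.

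**Working it through.** **Inputs (Sample size section).** SD of the 12-month VAS 30 mm. SD of duration 25, read as months because X is in months and the slope difference is per month. Correlation 0. Slope difference Δ = 4 mm per year = 4/12 = 0.3333 mm per month. Multipliers 1.96 and 0.84. Loss 10%, from the main-effect calculation.

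**Step 1: the plan's own figure.**
- σ = 30/25 = 1.2.
- n − 1 = (1.96 + 0.84)² × 2 × 1.2² / 0.3333² = 7.84 × 2.88 / 0.1111 = 203.2.
- n = 204.2 per arm, or 205 rounded up.

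The stated 200 is about 2% lower, so the figure is reproduced, as a number of evaluable patients.

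**Step 2: power.** The standard error of the slope difference is 1.2 × √(2/(n − 1)), and power = Φ(Δ/SE − 1.96).

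| Analysed per arm | SE | Δ/SE | Power |
|---|---|---|---|
| 200 (no loss) | 0.1203 | 2.771 | 79.1% |
| 190 (5% loss) | 0.1234 | 2.700 | 77.0% |
| 180 (10% loss) | 0.1268 | 2.628 | 74.8% |
| 170 (15% loss) | 0.1305 | 2.553 | 72.4% |

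A noncentral t calculation gives 74.6% at 180 per arm. The rounding costs under one point (79.1% against 80%). The 10% loss costs the other 4.3 points (79.1% to 74.8%).

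**Step 3: slope difference detectable with 80% power at 180 per arm.** 12 × 2.8 × 0.1268 = 4.26 mm per year, against the stated 4.

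**Step 4: number that would keep 80% after 10% loss.** 205/0.9 = 227.8, so 228 per arm or 456 in total.

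**Step 5: dependence on the VAS SD.** 180 per arm, duration SD 25, correlation 0.

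| VAS SD (mm) | Power |
|---|---|
| 30 | 74.8% |
| 28 | 80.4% |
| 27.5 | 81.8% |
| 25 | 88.4% |

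**Step 6: dependence on the correlation.** 180 per arm, VAS SD 30. Power is 75.2% at 0.1 and 76.5% at 0.2, the two values the section mentions.

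**Step 7: dependence on the duration SD.** 180 per arm, VAS SD 30. The required n varies as one over the square of this SD, so the cautious direction is downwards. SDs other than 25 are assumptions made only to show the slope: 20 months gives 56%, 26.7 gives 80%, and 30 gives 88%.

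**Step 8: main comparison with 180 per arm.** 15 / (30 × √(2/180)) = 4.743, and Φ(4.743 − 1.96) = 99.7%.

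**The case against.** The strongest reply is that 75% is a worst case. The plan calls an SD of 30 the worst case within its range of 25 to 30. After 10% loss the stated 80% still holds for any VAS SD up to about 28 (step 5), which is more than half of that range. This stands. The 75% has to be quoted with its conditions, not as a fixed property of the design. It does not remove the point: the plan states 80% at an SD of 30, and at that SD the figure fails once its own loss is applied.

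Second, the Statistical analysis section answers the duration question by extending a linear mixed model over all visits. Patients who miss month 12 would still contribute earlier data, so counting 180 complete cases may be pessimistic. This is fair, but the gain cannot be computed from the document and the sample size calculation takes no credit for it. A non-zero correlation helps too, but at the values mentioned it does not restore 80% under 10% loss (step 6).

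Three stronger readings are tempting and not supported:

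- **That 200 is itself a calculation error.** It is 2% below the formula result and costs under one point of power. A correlation of 0.15 would bring 200 analysed per arm back to 80.0%.
- **That calling the duration SD conservative is wrong.** The cautious direction is indeed a low value, but 25 may be low relative to the cited trial, which is not at hand. Nothing in the document shows that 25 is too high. Much lower power figures come only from SDs that the document does not give.
- **That the definition of duration reduces power.** Weeks against months is a change of unit. Time since the first general practitioner visit is a different starting point from duration of pain, but its effect on the SD, and so on power, cannot be computed. It is a separate inconsistency.

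**Conclusion.** The point holds in limited form. The calculation that sets the trial size carries no loss allowance, although the section assumes 10% loss elsewhere. With 180 analysed per arm, VAS SD 30, duration SD 25 months and zero correlation, power for 4 mm per year is about 75% instead of 80%. That is a shortfall of about five points, or a detectable difference of about 4.3 instead of 4 mm per year. It disappears if the VAS SD is about 28 or lower.

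A reader might infer that the trial as a whole is underpowered. It is not: the main comparison at one year stays above 99%. Severity is minor to moderate: one interaction question is affected, and the remedy is a matter of wording.

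**What to change.** Keep 400 patients and restate the figure, for example: 400 randomised, 10% loss, 180 analysed per arm; about 75% power for 4 mm per year at a VAS SD of 30 (80% for 4.3 mm per year). Add the power over the plan's VAS SD range: about 82% at 27.5 and 88% at 25.

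For the duration SD, say that the cautious direction is a low value. Then either justify 25 from its source or show power on both sides of it.

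Reconcile the two definitions of duration, in Sample size (months of pain before randomisation) and in Primary outcome measure (weeks since the first general practitioner visit), so that the SD used for sizing describes the variable that is analysed.

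The cost is a few sentences and a slightly less favourable power statement. No extra patients are needed. Holding 80% at an SD of 30 with 10% loss would instead take 456 patients, which a shortfall of this size hardly justifies.
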